# Protocol for understanding acute sarcopenia: a cohort study to characterise changes in muscle quantity and physical function in older adults following hospitalisation

**DOI:** 10.1186/s12877-020-01626-4

**Published:** 2020-07-10

**Keywords:** Acute sarcopenia, Physical function, Older adults, Hospitalisation

## Abstract

**Background:**

Older adults are vulnerable to the effects of acute sarcopenia (acute muscle insufficiency) following hospitalisation. However, this condition remains poorly characterised to date. It is hypothesised that acute sarcopenia arises due to a combination of bed rest and inflammatory surge. This study aims to characterise changes in muscle quantity and function, determining which factors (clinical and biological) are most predictive, and how these relate to change in physical function at 13 weeks.

**Methods:**

This study will include three groups of patients aged 70 years and older; patients undergoing elective colorectal surgery, patients admitted for emergency abdominal surgery, and patients admitted under general medicine with acute bacterial infections. Changes in muscle quantity (Bilateral Anterior Thigh Thickness with ultrasound and bioelectrical impedance analysis) and muscle function (muscle strength, physical performance) within 1 week of hospitalisation or surgery will be characterised, with follow-up of patients at 13 weeks. Physical function will be measured using the Patient Reported Outcome Measures Information System, and the Short Physical Performance Battery (or gait speed alone within 1 week of surgery).

**Discussion:**

This study will fully characterise changes in muscle quantity and function in hospitalised older adults and enable risk stratification towards targeted interventions in clinical practice. The results of this study will inform further research involving interventions to ameliorate changes.

**Trial registration:**

ClinicalTrials.gov Identifier: NCT03858192; Prospectively registered 28th February 2019.

## Background

Acute sarcopenia is an emerging condition of acute muscle insufficiency; older adults are considered particularly vulnerable to its effects following hospitalisation [1]. The European Working Group on Sarcopenia in Older People 2 (EWGSOP2) defines sarcopenia as reduced muscle strength with reduced muscle quantity or quality; cut-off values to meet criteria are usually set 2.0–2.5 standard deviations below the mean of a young adult healthy reference population. Additional demonstration of low physical performance is defined as severe sarcopenia. The revised definition (EWGSOP2) includes a distinction between acute and chronic sarcopenia; acute sarcopenia is defined as incident sarcopenia within 6 months, normally following a stressor event [2]. However, acute sarcopenia has been poorly characterised to date [1].

The biological mechanisms, clinical risk factors, longer term outcomes, and most effective management strategies of acute sarcopenia are currently unknown. Acute sarcopenia is considered to be caused by a combination of heightened inflammation and muscle disuse during bedrest. Studies involving healthy volunteers have demonstrated that bedrest is associated with declines in muscle quantity, strength, and aerobic performance, and that this effect is exacerbated by age [3, 4]. Acute illness (e.g. acute bacterial infection) and major surgery are associated with systemic inflammatory response [5] and endocrinological stress response (e.g. increased cortisol, decreased dehydroepiandrosterone sulfate (DHEA-s)) [6]. Pro-inflammatory cytokines activate pathways leading to increased muscle protein degradation [7] and hypercortisolaemia has been shown to exacerbate loss of muscle quantity during bedrest [8]. It has been postulated that acute sarcopenia may be partially recoverable, but may increase the risk of chronic sarcopenia over time [1]. It is proposed to be related to a combination of acute inflammatory surge and bedrest during hospitalisation [1]. Characterising acute sarcopenia will enable greater understanding of the significance of changes in clinical practice, and allow risk stratification towards targeted interventions.

EWGSOP traditionally recommended Computed Tomography (CT), Magnetic Resonance Imaging, or Dual-Energy X-Ray Absorptiometry to measure muscle quantity [9]. However, these tests cannot be used at the bedside and have limitations when used serially [10]. Ultrasound measurement of Bilateral Anterior Thigh Thickness (BATT) has excellent inter-rater and intra-rater variability [11]. EWGSOP2 supports use of ultrasound for clinical assessment of sarcopenia [2] and a consensus protocol has been proposed [12]. Bioelectrical Impedance Analysis (BIA) is an alternative non-invasive tool that provides estimates of lean mass. Muscle quantity measured by BIA has been shown to correlate with BATT [13], however, BIA is more greatly affected by fluid balance [14, 15]. BIA is also not currently recommended for use on people with implantable cardiac devices, although research suggests this is likely to be safe [16].

Colorectal surgery is commonly performed on older adults [17]. It is not typically associated with cachexia, when performed for localised colorectal cancer [18]; metastatic cancer is known to be associated with increased risk of cachexia compared to localised cancer [19]. Colorectal surgery patients do not typically present with disease-associated pre-operative functional decline associated [20], as compared to orthopaedic or vascular surgery, where impairments in function are presenting symptoms of the illnesses themselves [21, 22]. This offers the opportunity for pre-insult measurements to be taken prior to hospitalisation. Previous studies have demonstrated acute declines in handgrip strength and muscle quantity using BIA in older adults admitted electively for colorectal surgery [23]. Acute reductions in BATT and usual gait speed were also demonstrated in our pilot study, which was used to refine this protocol [24]. Interestingly, an apparent increase in BATT was demonstrated immediately postoperatively [24]; this may be related to fluid balance but warrants further investigation [25]. However, emergency admitted patients may be at the greatest risk of declines in muscle quantity and function due to increased inflammation. Within the UK, hospitalised older adults are most commonly admitted to general medicine wards [26]. Studies involving medical and orthopaedic patients have shown variable changes in muscle quantity and function in hospitalised older adults [23, 27, 28], and changes have not been evaluated in patients admitted for emergency abdominal surgery.

## Methods

### Aim

To clinically and biologically characterise acute sarcopenia in older hospital populations, assessing for within group differences in elective colorectal surgery, emergency surgery, and general medicine patients. This will enable determination of mechanisms and identification of potential intervention strategies.

### Design and setting

This is a single site cohort study at the Queen Elizabeth Hospital Birmingham (QEHB), involving 56 elective colorectal, 56 emergency abdominal surgery, and 56 medical patients. QEHB is a large tertiary hospital, with a firmly embedded research infrastructure. In the elective cohort, measurements will be performed in preoperative assessment clinic, within 48 h of surgery, at 7 days postoperatively (+/− 2 days), and at 13 weeks postoperatively (+/− 1 week). In the emergency surgery cohort, we aim to recruit participants preoperatively where possible. Where this is not possible, we will recruit participants within 48 h of emergency surgery; further assessments will be performed at 7 days postoperatively (+/− 2 days), and at 13 weeks postoperatively (+/− 1 week). Medical patients will be recruited within 48 h of admission with further assessment at 7 days post-admission (+/− 2 days), and at 13 weeks post-admission (+/− 1 week). The timeframe of 13 weeks has been chosen pragmatically as a timeframe that was considered important to our patient and public involvement panel that could be feasibly conducted without high drop-out rates. The full study schema is shown in Fig. 1.

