### Processes and interventions

Table 1 shows the complete schedule of assessments that will be performed during this study. We describe the procedures that will be performed at each visit in further detail below.

**Table 1 Tab1:** Schedule of study procedures. This chart shows all possible visits for each cohort and assessments that would be expected to take place for each participant in each cohort. Visits marked with * may not take place for all participants

Visit	Elective cohort				Emergency cohort				Medical cohort		
	A	B	C	D	A*	B	C	D	B	C	D
**Demographics, observations, medications, medical history, blood tests as part of routine care**	**✓**	**✓**	**✓**		**✓**	**✓**	**✓**		**✓**	**✓**	**✓**
**Review of CT scans performed as part of routine clinical care (if available)**	**✓**				**✓**						
**BATT using ultrasound**	**✓**	**✓**	**✓**	**✓**	**✓**	**✓**	**✓**	**✓**	**✓**	**✓**	**✓**
**BIA**	**✓**	**✓**	**✓**	**✓**	**✓**	**✓**	**✓**	**✓**	**✓**	**✓**	**✓**
**Handgrip strength**	**✓**	**✓**	**✓**	**✓**	**✓**	**✓**	**✓**	**✓**	**✓**	**✓**	**✓**
**Short Physical Performance Battery**	**✓**			**✓**				**✓**	**✓**	**✓**	**✓**
**Gait speed alone**			**✓**				**✓**				
**Physical function by PROMIS**	**✓**		**✓**	**✓**	**✓**		**✓**	**✓**	**✓**	**✓**	**✓**
**Katz ADLs and Lawton IADLs**	**✓**		**✓**	**✓**	**✓**		**✓**	**✓**	**✓**	**✓**	**✓**
**Mini Nutritional Assessment (Full)**	**✓**			**✓**	**✓**			**✓**	**✓**		**✓**
**Extra frailty assessments**	**✓**		**✓**	**✓**	**✓**		**✓**	**✓**	**✓**	**✓**	**✓**
**Venepuncture (optional)**	**✓**	**✓**			**✓**	**✓**			**✓**		
**Application of physical activity recorder (optional)**		**✓**				**✓**			**✓**		
**Delirium assessment**		**✓**	**✓**		**✓**	**✓**	**✓**		**✓**	**✓**	
**Fluid balance assessment**		**✓**	**✓**		**✓**	**✓**	**✓**		**✓**	**✓**	
**Participant feedback**				**✓**				**✓**			**✓**

*PROMIS* Patient Reported Outcome Measures Information System, *ADLs* Activities of Daily Living.

Visit A: Preoperative assessment; in preoperative assessment clinic for elective cohort, on ward prior to surgery for emergency surgery cohort (where possible) – not applicable to medical cohort.

Visit B: Immediate; Within 48 h of surgery for surgical cohorts, within 48 h of admission for medical cohort.

Visit C: One week; 7 (+/− 2) days after surgery (surgical cohorts) or after admission (medical cohort).

Visit D: Three months; 13 (+/− 1) week after surgery (surgical cohorts) or admission (medical cohort).

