### Data analysis

Data analysis will be conducted using IBM SPSS® Version 22. Results for each cohort will be analysed separately, although secondary data analysis will be conducted on all groups together. Interim analysis is planned with involvement from a patient and public involvement panel. Outcomes will be summarised at baseline, 7 days postoperatively, and 13 weeks postoperatively. The data analysis of the primary research question will include the following models:
Unadjusted model with PROMIS at 13 weeks as the outcome of interest, and the secondary outcome as the covariate of interest (i.e. change in BATT, handgrip strength and/or gait speed from baseline to 7 days).Adjusted model with PROMIS at 13 weeks as the outcome of interest, and the secondary outcome as the covariate of interest (i.e. change in BATT, handgrip strength and/or gait speed from baseline to 7 days), with adjustment for the baseline PROMIS score, and patient demographics (e.g. age, gender).Model with PROMIS at 13 weeks as the outcome of interest, with adjustment for baseline PROMIS, and all secondary outcomes as covariates to establish the strength of association between those secondary outcomes and the primary outcome. This model will be used to establish which of the secondary outcomes (i.e. change in BATT, handgrip strength and/or gait speed from baseline to 7 days) is most strongly associated with change in PROMIS at 13 weeks.

Change in PROMIS rather than change in SPPB, which can be considered an objective measure of physical function, has been selected as our primary outcome for two reasons. Firstly, our patient and public involvement panel considered their own perception of their physical function to be most important. Although perception of function may differ from objective function, how function is perceived for them as individuals was considered more important. Secondly, it will only be possible to obtain true pre-hospitalisation measures of SPPB for the elective cohort. PROMIS provides a method of evaluating physical function prior to admission in the emergency cohorts. Change in SPPB will be evaluated as a secondary outcome in the elective cohort.

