### Acute sarcopenia

Sarcopenia will be defined as per EWGSOP2 as handgrip strength below 16 kg in women or below 27 kg in men [2, 55], in combination with low muscle quantity or quality. Cut-offs for low muscle quantity and quality will be evaluated comparing the cohort against reference data in healthy young adults; cut-offs for BATT of 3.85 cm in women and 5.44 cm in men have been proposed [11]. Severe sarcopenia will be defined as additional presence of low physical performance; gait speed 0.8 m/s or less [56] or SPPB of 8 or less [57]. Acute sarcopenia will be defined as incident sarcopenia compared to baseline measurements at recruitment. The prevalence of sarcopenia will be calculated at each visit.

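### In the emergency surgery cohort, baseline is pre-operative for some patients and post-operative for others, so 7-day BATT change and incident sarcopenia partly reflect when the patient was first measured

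*Protocol article*

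**What the plan says.** All references are to the protocol article.

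- **Emergency cohort, first measurement.** Design and setting gives two routes: "In the emergency surgery cohort, we aim to recruit participants preoperatively where possible", and otherwise "Where this is not possible, we will recruit participants within 48 h of emergency surgery". Table 1 (Processes and interventions) marks the emergency cohort's Visit A with an asterisk, explained as "Visits marked with * may not take place for all participants". BATT, BIA and handgrip are scheduled at Visits A*, B and C.
- **Other cohorts.** Elective patients are first measured in the pre-operative clinic; of this group the Background says "This offers the opportunity for pre-insult measurements to be taken prior to hospitalisation". For the medical cohort, "Medical patients will be recruited within 48 h of admission".
- **Use of baseline.** All three models in Data analysis use change in BATT, handgrip and/or gait speed from baseline to 7 days as covariates for PROMIS at 13 weeks. The section Acute sarcopenia states: "Acute sarcopenia will be defined as incident sarcopenia compared to baseline measurements at recruitment".
- **Known post-operative effect.** The Background reports of the pilot that "an apparent increase in BATT was demonstrated immediately postoperatively", and suggests fluid balance as a possible cause.
- **Known baseline problem.** Data analysis notes that "it will only be possible to obtain true pre-hospitalisation measures of SPPB for the elective cohort", and evaluates change in SPPB in the elective cohort.

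**The concern.** Within the emergency cohort, a patient seen at Visit A starts from a pre-operative BATT. A patient first seen at Visit B may start from a value raised by the operation and fluids. Two patients with the same true course can then show different 7-day changes. The plan treats these as one variable in the cohort's main models and as one baseline for incidence. The listed models contain no term for baseline timing or fluid status, and the limitations in the Discussion do not mention the issue.

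Three results are exposed: the mean BATT loss reported for the cohort, the coefficient relating BATT change to 13-week PROMIS, and the incidence of acute sarcopenia. Handgrip has the same mixed start, but a first measurement taken soon after surgery could already be low, which would make the loss look smaller.

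**Working it through.** **1. The yardstick.** Power calculation gives a BATT target of 0.66 cm with SD 1.1 cm, 45 evaluable patients per group, paired t-test, 80% power and 5% significance, in both directions. Reading 1.1 cm as the SD at each visit with zero within-patient correlation, the SD of change is 1.1 × √2 = 1.56 cm. The noncentral t then gives n = 46, with 79.5% power at 45. The normal approximation gives 2 × (1.960 + 0.842)² / 0.6² = 43.6, so 44. The stated 45 is reproduced closely enough, and 0.66 cm is used below as the yardstick.

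**2. Inputs not in the documents.** These are the post-operative rise δ and the share q of emergency patients first measured at Visit B. Assumed: δ = 0.2 to 0.6 cm and q = 50% or 75%.

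**3. Shift in mean 7-day loss, against a pre-operative baseline.** Shift = q × δ.

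| q | δ = 0.2 cm | δ = 0.6 cm |
|---|---|---|
| 50% | 0.10 cm (15% of 0.66) | 0.30 cm (45%) |
| 75% | 0.15 cm (23%) | 0.45 cm (68%) |
| 100% | 0.20 cm (30%) | 0.60 cm (91%) |

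The last row is what results if everyone is analysed from Visit B and the result is read as loss from the pre-operative level.

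**4. Effect on the paired test.** Take δ = 0.3 cm and q = 50%, a shift of 0.15 cm, with no true change from the pre-operative level. At n = 45 the test rejects in 9.7% of studies instead of 5% if the within-patient correlation is 0, and in 20.6% if it is 0.7.

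**5. Spread added to the covariate.** Added SD = δ × √(q(1 − q)). At q = 50% this is 0.10 cm for δ = 0.2 and 0.30 cm for δ = 0.6. As a share of the variance of BATT change, if 1.1 cm is taken as the SD of change:
- δ = 0.6: 0.09 / (1.21 + 0.09) = 7%
- δ = 0.2: 0.01 / (1.21 + 0.01) = 0.8%

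If 1.1 cm is the SD at each visit and the correlation is 0.7, the variance of change is 2 × 1.21 × 0.3 = 0.726, and the share at δ = 0.6 is 0.09 / 0.816 = 11%.

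**6. Incident sarcopenia, muscle-quantity part only.** Take a normal distribution with mean 3.6 cm and SD 1.1 cm (Power calculation) and the women's cut-off of 3.85 cm (Acute sarcopenia). The share with low BATT at the first visit is Φ((3.85 − 3.6 − δ) / 1.1):
- δ = 0: 59%
- δ = 0.1: 55%
- δ = 0.3: 48%
- δ = 0.5: 41%

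At δ = 0.5 cm, 59 − 41 = 18 percentage points of existing low BATT would be missed at a post-operative baseline and could appear as new once the swelling resolves. This is illustrative: the mean is not sex-specific, and sarcopenia also requires low handgrip. Low handgrip at a post-operative first visit, or onset before recruitment, works the other way by making true new cases look prevalent.

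**The case against.** **The size is unknown.** The protocol calls the rise only apparent, and describes the pilot in its discussion of elective colorectal surgery. Emergency patients may already have disturbed fluid balance before the operation, so the step from Visit A to Visit B may differ. This stands, and it is why only a range is given. The variance share in step 5 is also modest.

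**Part of this belongs in an analysis plan.** Data analysis does not map baseline to a visit, and an SAP might do so. That is fair for the change scores. It does not cover the sarcopenia definition, which the protocol ties to recruitment.

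**The protocol is aware of the issue.** It chose PROMIS partly because a pre-admission state can be reported, flags the BATT rise for investigation, and records fluid status at every in-hospital visit. This protects the outcome more than the covariate, and no adjustment is named.

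**Stronger readings that the documents do not support:**
- *Acute sarcopenia is undercounted.* A raised first BATT creates false new cases, while low handgrip or onset before recruitment hides true ones. The balance cannot be determined.
- *Change in gait speed is affected in the emergency cohort.* The section Physical performance says gait speed is not measured at recruitment there, so no such change score exists.
- *Differences between cohorts bias the main results.* Each cohort is analysed separately, so mixing across cohorts affects only the pooled secondary analysis.
- *Timing of recruitment tracks urgency and so confounds the association with PROMIS.* This is plausible, but no passage establishes it.
- *Starting everyone at Visit B removes the bias.* It makes the start uniform within the cohort, but the shift against the pre-operative level becomes the full δ.

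**Conclusion.** The point holds for the emergency surgery cohort. Following the text as written puts two non-equivalent starting points into one change score and one incidence definition, and the protocol's own pilot gives the reason to expect a difference in BATT. With an assumed rise of 0.2 to 0.6 cm and half of patients first measured after surgery, mean 7-day BATT loss against a pre-operative baseline is overstated by 0.10 to 0.30 cm, 15 to 45% of the 0.66 cm target. The true figure could lie outside this range, because neither input is in the documents. No direction can be given for incident sarcopenia. The effect on the regression coefficient is probably small if timing is unrelated to outcome, and unknown if it is related. This should be corrected before analysis, but it does not undermine the elective or medical cohorts' own results on change.

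**What to change.** 1. **Define baseline by visit relative to surgery or admission.** Elective: Visit A. Medical: Visit B.
2. **Emergency cohort.** Do not pool first measurements from A and B as one baseline. Either report change from A (pre-operative subset) and from B (all patients, already in Table 1) separately, or include a baseline-timing indicator and its interaction with change. State that B-to-C change starts from a possibly fluid-raised value and is not loss from the pre-operative level.
3. **Sensitivity analysis.** Adjust for the recorded fluid status.
4. **Pooled secondary models.** Include cohort and cohort-by-change terms.
5. **Incident sarcopenia.** Report it separately by whether the baseline preceded the insult, and label the rest *new since first in-hospital assessment*. Show emergency patients seen at Visit A on their own line, since that visit precedes the operation but not the admitting illness.

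The cost is wording and additional analyses; no new measurement is needed. The drawback is low precision in the pre-operative emergency subset, whose size is not known in advance.

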**Fig. 1 Fig1:**
[figure not shown]
Study schema for recruitment and follow-up of each included cohort

### Characteristics of participants

The elective cohort will include patients expected to undergo major colorectal surgery, the emergency surgery cohort will include emergency admitted patients who have undergone or are planned to undergo emergency abdominal surgery, and the medical cohort will include emergency admitted patients with (or suspected) acute bacterial infections. Participants aged 70 years or older at time of recruitment will be included in all cohorts. Participants who are unable to provide written informed consent at time of recruitment will not be included in the elective cohort, although specific consent will be obtained for participants to remain in the study if they lose capacity, including details of any named consultee. In the emergency surgery and medical cohorts, personal or professional consultee declaration will be obtained if the participant is unable to provide written informed consent. Participants who are unable to understand verbal English, who were unable to mobilise prior to admission to hospital, or who have a life expectancy of less than 30 days will be excluded from all cohorts.

